### Expected duration of trial

The trial is expected to recruit for 3 years. We estimated that the minimum number of individuals in each of groups C and D still HLA Ab– at the primary end point should be 627 (see Figure 
1). The recruitment target is to randomise 950 patients to each of these groups. This allows for the predicted dropout rate and the rate of antibody conversion with a margin of error. Patients will be followed up for a period of 3 years post-recruitment, except for patients in groups C and D who become Ab + during the initial 3 years of follow-up, who will transfer to the relevant Ab + group and be followed up for a further 3 years from the date of transfer. Therefore, the maximum amount of time that any single patient can remain in the study is 6 years. Communication of the need for an extended follow-up will be made at the final HLA screening round at month 32, after the primary outcome data have been collected, to avoid unblinding the HLA status in the blinded care arm.

### Trial procedures

#### Synopsis

A structured screening programme for IgG HLA Ab is proposed in patients who provide consent. Results obtained will initially be blinded to the transplant clinicians and patients. Patients will be randomised through the King’s Clinical Trials Unit and stratified: (1) DSA+, non-DSA + or HLA Ab–, (2) by current immunosuppression (tac alone, MMF alone, both tac and MMF, or neither tac nor MMF) and (3) recruiting study site. Patients in groups A1, A2 and C (see flow diagram in Figure 
1) will remain blinded to the results of their screening (as will their clinicians), whereas those in B1, B2 and D will learn whether they are HLA Ab + or Ab–. All recruits will undergo a final test for HLA Ab status as they reach the end of the study. The optimised treatment protocol for patients in the two groups with HLA Ab (B1 and B2) is outlined above. Patients in all groups will have blood pressure controlled and total cholesterol lowered, according to local unit guidelines.

#### First visit

Post consent, patients who have not been screened for HIV or hepatitis B/C within the last 5 years will undergo additional screening tests for these viruses. Female patients who report they may be pregnant will have a blood test for beta-Human Chorionic Gonadotrophin levels. Once eligibility criteria have been met, the following baseline data will be recorded at recruitment:

• Weight

• Blood pressure

• Sex

• Ethnicity

• Age

• Date of birth

• HLA type

• HLA type of donor kidney (if known)

• Any significant past medical history, including history of diabetes mellitus, cause of renal failure, details of previous transplants and cause of graft loss, evidence of sensitisation pre-transplantation (panel reactive antibody and antibody specificities if known)

• Medication including doses

• PCR of urine sample

All patients will then have blood taken for;

• Baseline clinical parameters: full blood count (minimum haemoglobin, white cell count, platelets); biochemical series (creatinine, Na^+^, K^+^, bicarbonate, calcium, C-reactive protein, lipid profile, glucose); MDRD eGFR on latest creatinine; current calcineurin inhibitor 12-hour trough levels (as appropriate); total immunoglobulin levels

• Scientific analyses: 50 to 60 mL blood for separation of peripheral blood mononuclear cells (PBMC) and 20 mL for serum storage

• Analysis of HLA Ab status (10 mL clotted blood), as described above, which will allow randomisation to proceed

All patients will be asked to complete questionnaires to assess attitudes to risk and adherence.

#### Subsequent visits

The optimised treatment protocol will be introduced within the first 3 months in those HLA Ab + patients allocated to this group. Recruits will be seen up to every two weeks during this period (a maximum of six extra clinic appointments are envisaged), though they should be on a maintenance dose of prednisolone 7 weeks after initiating optimisation. During this period they will have full blood count (as above), creatinine, Na^+^, K^+^, glucose, calcineurin inhibitor trough levels and blood pressure monitored according to the trial protocol. Once stabilised, they will be seen at least every 4 months in the transplant clinic. Patients allocated to all other groups will be seen at least every 4 months in the transplant clinic for formal study assessments. Patients may be seen at other times during this period, according to clinical need, but study assessments should be done within the time parameters established in the protocol.

Once every 4 months the following will be recorded:

• Weight

• Blood pressure

• Full blood count (minimum haemoglobin, white cell count, platelets)

• Biochemical series (creatinine, Na^+^, K^+^, bicarbonate, calcium, C-reactive protein, glucose)

• MDRD eGFR on latest creatinine

• Calcineurin inhibitor trough levels

• PCR of urine sample

• Total immunoglobulin levels

• Episodes of infection, malignancy or new DM

• Episodes considered to be adverse events

Every 12 months, each patient’s lipid profile will be measured.

For all patients with HLA Ab, and a small cohort of patients without, separate blood samples will be taken for non-routine scientific analyses as above. Steps will be taken to ensure this sampling does not break the blinding of group allocations. Once every 8 months, HLA Ab– patients will undergo further screening for HLA Ab (see above). At the end of the study, all patients will undergo a final test for HLA Ab status.

In recruits with living donors (known to them), the living donors will be invited to participate either by the recruit or directly by the study team, following consent from the recruit to inform donors of their participation in the study. Donors will attend the clinic at their convenience, where consent will be taken and blood (60 mL) taken for separation of PBMC, which will be stored in the research laboratory, identified only as from the donor of a particular study recruit. Donors may be asked to donate another aliquot of blood at another time within the next 3 years.

### Laboratory tests

#### Human leukocyte antigen antibody analysis

Serum prepared from 10 mL of blood will be used in the commercially available LABScreen tests (One Lambda, Canoga Park, CA), containing fluorescently tagged beads coated with purified HLA antigens. All participating centres have Luminex equipment (Luminex Corp, Austin, Texas) for analysis of these tests and the skills to process samples and interpret results. Therefore, the tests will be performed in each of the centres. A sequential analysis of samples is planned, first to identify those with HLA Ab, using mixed class I and class II Ab screening beads coated with multiple different types of HLA. The manufacturer’s definition of positive and negative tests will be used when interpreting the results. In those patients with positive results, the specificity of the HLA Ab will be determined by SAB, coated with single HLA class I or class II antigens. As before, when interpreting the results, the manufacturer’s definition of positive and negative tests will be used. Any patient with a positive test for HLA Ab identified by SAB will be regarded as HLA Ab + for the trial if the mean fluorescence intensity (MFI) is ≥2,000. If the HLA Ab are directed against a mismatched donor HLA antigen, the patient will be assigned as DSA+. The number of DSA with MFI ≥ 2,000 will be used to define the Ab ‘burden’ of an individual. In the final analysis, correlations between HLA Ab burden and outcomes will be sought. Patients with SAB positivity that is difficult to label as DSA + or non-DSA + (because of insufficient data on donor mismatches, for instance), will be regarded as being non-DSA+. Patients with a positive reaction on screening but lacking reactivity with the SAB at the level described will be considered negative. Excess serum will be stored. The same screening will be undertaken for HLA Ab– patients every 8 months, with the samples taken at a routine clinic appointment.

#### Routine biochemical, haematological and calcineurin inhibitor trough analysis

These will be performed by the local clinical laboratories and the results recorded as above.

#### Scientific laboratory analysis

A laboratory analysis will be performed at recruitment for all patients and then every 4 months on patients with HLA Ab and a small cohort of patients who are HLA Ab–, chosen randomly at randomisation. Then, 60 to 80 mL blood will be taken and 20 mL for serum. The samples will be sent to the research laboratory of the chief investigator where the blood will be separated into PBMC and CD34+ cells. DNA and RNA will be extracted from a small number of cells and stored. All other cells will be stored in aliquots in liquid nitrogen until thawed for analysis. Serum samples will be stored at -80°C until thawed for analysis. The same process for preparing PBMC will be used for the samples from donors.

Patients will also consent to analysis, for research purposes, of any stored serum, blood or tissue (such as transplant biopsies). This will apply for all existing and future samples taken for clinical reasons. In the case of future transplant biopsies, the patients will be asked to consent to having an extra core taken for transcriptome analysis. Subject to available funding, this will be stored in an appropriate medium and transported to the chief investigator’s laboratory for storage.

### Procedures for assessing efficacy parameters

Graft failure is defined as the return to long-term dialysis or re-transplantation. This will be measured from the date of recruitment and will be reported for failure due to any cause. The date of restarting dialysis or re-transplantation will be recorded on the Case Report Form.

Deteriorating renal function will be determined by linear regression analysis of the serial MDRD eGFRs from the point of recruitment (like that used by Dudley *et al*.
[14]). Deterioration is defined as a negative slope. To be valid, the linear regression should yield an adjusted *r*^2^ ≥ 0.35 and have *P* ≤ 0.05 for the slope value. Stable renal function will be defined as serial MDRD eGFRs that are not significantly different from the horizontal baseline (that is, *P* > 0.05 on linear regression analysis). An improvement in renal function will be defined as a change in the slope so that it becomes positive. Serum creatinine levels and MDRD eGFR for the 12 months preceding recruitment and for the whole time patients are on the trial will be recorded on the CRF.

Proteinuria is defined by the PCR of a urine sample and is significant if >50. The PCR will be recorded on the CRF.

Acute rejection is defined by a combination of: (a) an acute rise in serum creatinine prompting a renal biopsy and (b) any pathology on the biopsy that meets the criteria for acute rejection, according to the latest BANFF criteria. The number of biopsies and the appropriate biopsy reports will be recorded on the CRF.

A full economic evaluation will adopt a National Health Service (NHS) perspective. The 3-year outcomes are the rates of: (1) graft failure, (2) patient survival, (3) graft dysfunction (see definition above), (4) acute rejection and (5) culture-positive infection, malignancy or diabetes, together with (6) EQ-5D, which is a patient-specific quality-adjusted life years (QALY) measurement. Cost-effectiveness will use (1) to (5) where (1) is the primary and the others are secondary outcomes. Cost-utility will be measured using (6) (the EQ-5D questionnaire). The net benefit per patient will be calculated by multiplying QALY by the assumed maximum willingness-to-pay for QALY (£20,000 per QALY) and subtracting the costs. The costs of all interventions will be obtained from Guy’s or estimated by identifying relevant categories of resource utilisation or measuring the volume of each category and multiplying by the average NHS resource costs
[15] (and using British National Formulary and NHS reference lists). The costs of an intervention include the cost of screening beads and enhanced drug costs.

Participants’ reporting of adherence will be assessed using the Medicines Adherence Report Scale (MARS)
[16,17], a valid and reliable scale that has been previously used to assess adherence in renal transplant recipients
[18,19]. Self-report measures have the advantage of being inexpensive and non-intrusive. However, it is known that self-reporting underestimates the true extent of non-adherence because of inherent self-presentational and recall biases. Self-presentational bias occurs when respondents may be reluctant to admit to non-adherence because they perceive a social contract where the expectation is one of high adherence. MARS takes steps to diminish this bias by sanctioning and normalising reports of non-adherence. However, this does not totally remove the effect of self-presentational and recall biases that are inherent in all self-report measures. For this reason we will apply a combined approach to adherence assessment, where an initial categorisation of patients into high vs low on the basis of self-reporting is revised based on calcineurin inhibitor blood monitoring (carried out in routine management for patients prescribed tacrolimus or ciclosporin) and tablet counts (conducted for a sample of participants). In this approach, reports of low adherence are accepted as self-presentational biases that act in the opposite direction (reports of low adherence are more reliable than reports of high adherence
[20,21]). Patients who report high adherence are reclassified to low adherence on the basis of calcineurin inhibitor trough results (for example, if levels are undetectable then the participant is assumed to be non-adherent) or tablet counts (for example, if there is a greater than 20% discrepancy between the actual and expected tablet count then the participant is reclassified as non-adherent).

To explore the potential antecedents to participants’ adherence behaviours, they will be also be asked to complete specially adapted versions of questionnaires relating to treatment intrusiveness, symptoms associated with immunosuppressants, beliefs about medicines
[22], satisfaction with information about their medicines
[23] and whether they are feeling anxious and/or depressed
[24]. Questionnaires will be used to qualify perceptions of personal risk
[25]. On the basis of survey responses, a small number of participants will be purposively selected (for example, those with positive and negative attitudes, and high and low adherers) for qualitative interview to explore their perception of risk and adherence behaviours in more depth.

All patients taking part in the trial will be asked to complete all or some of the questionnaires at specified times. Questionnaires will be administered electronically. Respondents will complete a survey online whilst in a clinic, using an iPad or equivalent tablet device designated solely for this trial. Completed survey responses are stored on Qualtrics secure servers and can only be accessed using a login and password. Nothing will be recorded on the main trial CRFs.

The questionnaires will be piloted with the first few participants recruited to the Guy’s site. These respondents will be asked to undergo cognitive interviewing whilst completing the survey, a technique used to ensure the validity of questionnaire items
[26]. On the basis of this pilot, the questionnaire items may undergo minor modification. The ease of utility of the online survey and tablet device will also be evaluated during the pilot.

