**Methods/Design:**

Recipients >1 year post-transplantation, aged 18 to 70 with an estimated glomerular filtration rate >30 mL/min will be randomly allocated to blinded or unblinded screening arms, before being screened for the presence of antibodies. In the unblinded arm, test results will be revealed. Those with antibodies will have biomarker-led care, consisting of a change in their anti-rejection drugs to prednisone, tacrolimus and mycophenolate mofetil. In the blinded arm, screening results will be double blinded and all recruits will remain on current therapy (standard care). In both arms, those without antibodies will be retested every 8 months for 3 years. The primary outcome is the 3-year kidney failure rate for the antibody-positive recruits, as measured by initiation of long-term dialysis or re-transplantation, predicted to be approximately 20% in the standard care group but <10% in biomarker-led care. The secondary outcomes include the rate of transplant dysfunction, incidence of infection, cancer and diabetes mellitus, an analysis of adherence with medication and a health economic analysis of the combined screening and treatment protocol. Blood samples will be collected and stored every 4 months and will form the basis of separately funded studies to identify new biomarkers associated with the outcomes.

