### Primary end points

The primary end point is the 3-year graft failure rate in HLA Ab + patients. Graft failure will be defined as restarting long-term dialysis or requiring a new transplant. Time zero starts at the time of randomisation, once the result of the HLA test is known. For those patients who are HLA Ab– at randomisation but become Ab + during a subsequent screening, time zero will be reset at the time of the positive test, and the follow-up time will be extended to allow for the 3-year end point.

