### Secondary end points

The secondary clinical end points are:

• 3-year graft failure rates in all patients recruited to the trial

• Patient survival

• Rate of progression of graft dysfunction, as assessed by the change in the degree of proteinuria (PCR > 50) or the change in estimated GFR over 3 years

• Rate of biopsy-proven rejection over 3 years

• Rates of culture- or polymerase chain reaction-positive infection, biopsy-proven malignancy and DM

• Health economic analysis of outcomes

• Analysis of adherence and perceptions of risk for the biomarker-led care (BLC) groups

• The secondary scientific end points are:

• Changes in characteristics of HLA Ab and laboratory parameters of T and B cell phenotypes and responsiveness for the HLA Ab + groups

• Change in numbers and phenotype of circulating CD34+ cells for the HLA Ab + groups

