In summary, this trial will identify a group of patients at high risk of premature transplant failure. Therapy will be optimised for these at-risk patients, many of whom will be identified before they have started to deteriorate clinically. As described above, the natural history of untreated CR is of progressive loss of function, usually at a predictable rate, leading eventually to complete loss of graft function. Depending on the initial creatinine level, the time to graft loss will be variable, but graft loss rarely occurs without this period of progressive loss of function. Lachmann *et al*.
[8] reported a constant rate of graft loss from the start of their study, so we expect that the rate of graft loss in our study will be constant in the standard care group. We predict that optimised immunotherapy will change the natural history of the condition, and lead to stabilisation of function in a significant proportion (50%) of those with HLA Ab. This will be visible in our analyses of the secondary end points. Hopefully the treatment will prevent the predicted graft loss in the first 3 years for this group and thus impact on the primary end point of the study.

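### The eGFR slope starts at recruitment even for patients who become antibody-positive later, so their fitted line mixes 8 to 32 pre-conversion months into the antibody-positive comparison

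*Protocol article*

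**What the plan says.** Under *Procedures for assessing efficacy parameters*, the article states: "Deteriorating renal function will be determined by linear regression analysis of the serial MDRD eGFRs from the point of recruitment". It adds: "Deterioration is defined as a negative slope", subject to thresholds for adjusted r² and P. Slopes that do not differ significantly from zero count as stable. *Secondary end points* lists "the change in estimated GFR over 3 years" without saying where the 3 years begin.

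The Abstract says that "those without antibodies will be retested every 8 months for 3 years", and *Expected duration of trial* puts the last round at month 32. Patients who convert are moved to the antibody-positive groups for the final analysis (*Trial design*). *Expected duration of trial* describes them as patients "who will transfer to the relevant Ab + group and be followed up for a further 3 years from the date of transfer".

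For graft failure, *Primary end points* says of these patients that "time zero will be reset at the time of the positive test". The efficacy-procedures section does not repeat this reset. Its own sentence on graft failure reads "This will be measured from the date of recruitment".

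**The concern.** A converter is antibody-negative and on existing immunotherapy in both arms until the positive result. In the unblinded arm that result triggers the treatment change. A line fitted from recruitment therefore runs through a first segment in which treatment cannot differ between arms and a second in which it can. A single slope averages the two.

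The protocol recognises this problem for graft failure and resets the clock, but the slope rule does not follow. The two sections thus use different time origins for the same patients in the same comparison. The Discussion predicts stabilisation of function in half of those with antibodies and says: "This will be visible in our analyses of the secondary end points". Graft dysfunction is also an outcome in the economic evaluation. An understated slope difference, or a label that reflects the period before treatment, would weaken the evidence on that prediction.

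**Working it through.** The article gives no power, effect size or sample size for the eGFR slope, so there is no figure of its own to reproduce.

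**Inputs from the article.** Conversion at months T = 8, 16, 24 or 32; eGFR every 4 months (*Subsequent visits*); 36 months of follow-up after conversion; 25% to 30% positive at baseline; 6% conversion and 2% dropout per round; 60% antibody-negative at the end (*Sample size calculations*).

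**Mean slope difference.** Assume the arm difference is zero up to T and then grows by 1 unit per month, d(t) = max(t − T, 0). The least-squares slope of d on t is Σ(t − t̄)d / Σ(t − t̄)². Fitted from the positive test, it equals 1. Fitted from recruitment:

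| T (months) | Months 0 to T + 36 | Months 0 to 36 |
|---|---|---|
| 8 | 2040/2288 = 89% | 1120/1320 = 85% |
| 16 | 2760/3640 = 76% | 760/1320 = 58% |
| 24 | 3480/5440 = 64% | 368/1320 = 28% |
| 32 | 4200/7752 = 54% | 72/1320 = 5% |

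**Share of converters.** There are two routes.
- Per-round rates: the antibody-negative pool shrinks by 0.94 × 0.98 = 0.9212 per round, and 1 + 0.9212 + 0.8486 + 0.7818 = 3.552. With 25% positive at baseline, converters are 0.75 × 0.06 × 3.552 = 0.160, and 0.160/(0.160 + 0.25) = 39%. With 30% they are 0.149, and 0.149/(0.149 + 0.30) = 33%. Ignoring dropout gives up to 40%.
- End-of-trial split (40% positive): (40 − 30)/40 = 25% to (40 − 25)/40 = 37.5%.

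The supported range is therefore about 25% to 40%.

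**Averages.** The round weights are 0.282, 0.259, 0.239 and 0.220.
- Converters, full follow-up: 0.282 × 0.892 + 0.259 × 0.758 + 0.239 × 0.640 + 0.220 × 0.542 = 0.72. Months 0 to 36: 0.47.
- Whole antibody-positive set, 1 − share × (1 − average), full follow-up: 1 − 0.40 × 0.28 = 0.89 to 1 − 0.25 × 0.28 = 0.93. Months 0 to 36: 1 − 0.40 × 0.53 = 0.79 to 1 − 0.25 × 0.53 = 0.87.

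**Per-patient label.** The article's rule was simulated with assumed values: after conversion a decline of 3 mL/min/year in control and none in treated patients, residual SD 4, between-patient slope SD 1.5. Follow-up ran to T + 36 months unless stated.
- The arm difference in the proportion labelled deteriorating is about 0.41 when fitted from the positive test. Fitted from recruitment it is about 0.31 to 0.48, depending on T and on the course before conversion (flat, or declining at up to the same 3 mL/min/year).
- Control patients who are flat and then decline, T = 32: 33% to 36% are labelled stable when fitted from recruitment, against 49% from the positive test.
- Treated patients who decline by 3 mL/min/year before conversion and then stabilise, T = 32: about 7% are labelled deteriorating when fitted from the positive test, against 35% to 40% from recruitment.
- With a 0 to 36 month window and a flat course before conversion, the arm difference falls to 0.32, 0.18, 0.07 and 0.01 for the four rounds.

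**The case against.** The strongest reply is that the recruitment wording is shorthand. The neighbouring graft-failure sentence uses the same origin and must already yield to the reset under *Primary end points*, so a reader could apply that reset to the slope too. This is plausible, but the text states the reset only for graft failure. The SAP may settle the matter, yet the article does not leave the origin open: it names one.

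A second reply is that the pooled loss is small. With extended follow-up it is 7% to 11%, on a secondary end point that carries no power calculation or formal hypothesis. That stands. The much larger losses need a window that closes 36 months after recruitment. Extended follow-up and the recording of eGFR for the whole time on trial speak against that reading, although the end point as worded does not exclude it.

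A reader might also infer that the rule pushes patients who decline after conversion into the stable category, and so shrinks the treatment effect on the label. The checks do not support this with extended follow-up. The longer series adds precision, fewer such decliners are called stable, and the arm contrast is similar or larger in many scenarios, falling short mainly for late converters. The inference holds only for the 0 to 36 month window with a flat course before conversion. Nor do the documents establish that converters are at least a third of the antibody-positive set; that is the upper part of the range.

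**Conclusion.** The point holds as an inconsistency of time origin with a calculable cost, and it should be corrected. For the mean slope difference, a fit from recruitment with full follow-up loses 11% to 46% of the effect in converters, depending on the round, about 28% on average and 7% to 11% over the antibody-positive set. With the 3 years counted from recruitment, the losses are about 53% in converters and 13% to 21% overall. These figures assume that the arm difference is zero until conversion and linear after it.

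For the per-patient label, the defect is one of meaning and not a consistent loss of contrast: patients who stabilise on treatment after an earlier decline are more often called deteriorating. The size of that effect rests on the assumed simulation values. Patients positive at baseline are not affected, and the primary hypotheses do not depend on the slope.

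**What to change.** For the antibody-positive comparison, state that the eGFR slope starts in both arms at the first positive result and runs to 36 months after it, in line with the reset under *Primary end points*. Use converters' earlier eGFRs only as a baseline segment or covariate. Keep the recruitment origin for the comparison of all randomised patients. State from which date the 3 years of the eGFR end point are counted, and bring the graft-failure sentence in the efficacy-procedures section into line with the reset.

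The change needs wording in the protocol or SAP and no new data, because eGFR is recorded throughout. The cost is a shorter series for each converter, about 10 values instead of 12 to 18 with full follow-up, and hence a less precise individual slope.

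### The renal-function categories treat a non-significant within-patient slope as stable function, whatever its size, and they do not cover every patient

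*Protocol article*

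**What the plan says.** The rule is in the protocol article, Procedures for assessing efficacy parameters. Each patient has one regression: "Deteriorating renal function will be determined by linear regression analysis of the serial MDRD eGFRs from the point of recruitment". Three labels follow.

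- Deteriorating: "Deterioration is defined as a negative slope", with the condition "To be valid, the linear regression should yield an adjusted *r*^2^ ≥ 0.35 and have *P* ≤ 0.05 for the slope value".
- Stable: "Stable renal function will be defined as serial MDRD eGFRs that are not significantly different from the horizontal baseline", which the article equates with P > 0.05.
- Improved: "An improvement in renal function will be defined as a change in the slope so that it becomes positive". No P value or r² is attached to this sentence.

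The section also has the CRF hold "Serum creatinine levels and MDRD eGFR for the 12 months preceding recruitment and for the whole time patients are on the trial". Its economic paragraph takes graft dysfunction, by reference to the definition above it, as one of the secondary cost-effectiveness outcomes.

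On visits, the section Subsequent visits states for patients outside the optimised-treatment groups: "Patients allocated to all other groups will be seen at least every 4 months in the transplant clinic for formal study assessments". For those starting optimised treatment it states: "Recruits will be seen up to every two weeks during this period (a maximum of six extra clinic appointments are envisaged", all within the first 3 months, with creatinine among the tests.

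Elsewhere, Secondary end points lists change in eGFR over 3 years, Secondary analysis gives a t-test for continuous outcomes, and Handling missing data fits linear mixed models to repeated measures.

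**The concern.** A P value above 0.05 in one patient's regression says that the data do not settle the direction of the slope. It does not say that the slope is small. With few values even a steep fall is non-significant, so a graft lost early can be labelled stable, and a slow true decline is often labelled stable after full follow-up.

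The labels also fail as a classification. A significant decline with adjusted r² below 0.35 is neither deteriorating nor stable, and the wording for improvement can be read as overlapping with stable.

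What is at stake is the categorical graft dysfunction outcome and its place in the economic evaluation. The Discussion predicts stabilisation in half of the HLA Ab+ patients and expects this to show in the secondary end points. A label of stable that means only not significant is poor evidence for that prediction.

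**Working it through.** The article gives no error rate or power for these categories, so there is no stated figure to reproduce. The cut-offs can be checked exactly. The misclassification rates need assumptions.

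**Inputs from the article.** P cut 0.05; adjusted r² cut 0.35; values every 4 months over 3 years, hence 10 values (months 0, 4, …, 36); up to 6 extra visits with creatinine in the first 3 months for treated patients, hence up to 16.

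**Assumptions not in the article.** Linear true decline and independent normal residuals, with a within-patient SD of 4 mL/min (range 2 to 6 for early loss, 3 to 6 for 3 years).

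**Step 1: what P ≤ 0.05 requires (exact).** With t = t(0.975, n−2), r² must reach t²/(t² + n − 2), and adjusted r² = 1 − (1 − r²)(n − 1)/(n − 2).

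| n | t | r² at P = 0.05 | \|r\| | adjusted r² |
|---|---|---|---|---|
| 3 | 12.706 | 0.994 | 0.997 | 0.988 |
| 4 | 4.303 | 0.903 | 0.950 | 0.854 |
| 9 | 2.365 | 0.444 | 0.666 | 0.365 |
| 10 | 2.306 | 0.399 | 0.632 | 0.324 |
| 16 | 2.145 | 0.247 | 0.497 | 0.194 |

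**Step 2: an early loss.** Take eGFR 45, 38, 15 at months 0, 4, 8. The slope is (15 − 45)/8 × 12 = −45 mL/min/yr. The total sum of squares is 492.67 and the residual sum is 42.67, so r² = 450/492.67 = 0.913 and t = √(450/42.67) = 3.25 on 1 degree of freedom. P = 0.19, so the label is stable. With 45, 42, 35, 12 over 12 months the slope is −31.8 mL/min/yr and P = 0.084, again stable.

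For a linear true loss of 30 mL/min/yr, the share labelled stable is:

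| Residual SD | 2 | 3 | 4 | 6 |
|---|---|---|---|---|
| 3 values | 58% | 71% | 78% | 85% |
| 4 values | 0.2% | 6% | 21% | 48% |

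**Step 3: slow decline over the full schedule.** For ten values, Σ(time − mean)² = 82.5/9 = 9.167 yr². At −3 mL/min/yr and SD 4 the non-centrality is 3 × √9.167/4 = 2.27, against a critical t of 2.306. The non-central t on 8 degrees of freedom gives 48% stable. At SD 3 it is 24%; at SD 6 it is 73%.

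**Step 4: the gap.** From Step 1, a significant decline can have adjusted r² below 0.35 only from n = 10 upwards: 0.324 to 0.35 at n = 10, 0.194 to 0.35 at n = 16. At −3 mL/min/yr and SD 4, with ten values, 48% are deteriorating, 48% stable and about 4% unclassified. With nine or fewer values there is no gap.

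**Step 5: conditional on the extra values being used.** Six fortnightly values in weeks 2 to 12 are added, the stated maximum, SD 4.

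| True slope (mL/min/yr) | Deteriorating, 10 v 16 values | Stable, 10 v 16 | Unclassified, 10 v 16 |
|---|---|---|---|
| 0 | 2.1% v 0.4% | 95% v 95% | 0.4% v 2.0% |
| −1 | 8.4% v 4.3% | 90% v 85% | 1.3% v 11% |
| −3 | 48% v 52% | 48% v 20% | 4% v 28% |
| −4 | 72% v 82% | 25% v 4% | 3% v 14% |

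The extra values raise the deteriorating rate at steep slopes and lower it at shallow ones.

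**The case against.** Five objections deserve weight.

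- **Which values count.** The article lists eGFR only among the 4-monthly records; the titration visits list creatinine. The CRF sentence gives a recording period, not the set of values for the regression. A reader might infer that the number of eGFR values differs by arm and that the rule is therefore biased between arms. The article does not say so. It leaves the question open, and even on that reading the direction changes with the slope. This objection stands, so the arm difference can be stated only conditionally.
- **Opposite assumptions.** The early-loss figures in Step 2 use scheduled values only; those for 16 values in Step 5 use the extra ones. They cannot both apply to a treated patient. With six extra values, the 78% stable at −30 mL/min/yr over 8 months (SD 4) falls to 4.5%. This stands, and the two sets must not be added together.
- **Size of the gap.** On scheduled values the unclassified share is small. This stands; the 28% belongs only to the conditional case.
- **Improvement.** The wording speaks of a change in slope, and eGFR from the year before recruitment is recorded, so it may mean a change from an earlier slope. The validity condition may also cover positive slopes. A reader might infer that nearly half of truly flat patients are both stable and improved, since about 47% have a non-significant positive slope. The text does not compel that reading; the point is ambiguity, not a proven contradiction.
- **Consequence.** Graft failures still count in the primary end point and the primary cost-effectiveness outcome, and the t-test and mixed models remain available for eGFR. This stands and limits the harm.

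The analysis plan may add a minimum number of values or rules for failed grafts. That does not answer the main point, because the article itself fixes the cut-offs and the meaning of stable.

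**Conclusion.** The concern holds for the categorical rule. Calling any P > 0.05 stable is unsound whatever the SD, and the |r| thresholds, the worked early-loss examples and the existence of the gap are exact. The rates are not: about 48% of patients losing 3 mL/min/yr labelled stable, and about 4% unclassified, rest on ten values, linear decline and an assumed SD of 4 mL/min; across SD 3 to 6 the stable share runs from 24% to 73%. Mislabelling of rapid loss is common with three values; with four it depends on noise and on how straight the fall is.

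A dependence on arm follows only if the titration creatinines enter the regression, and no consistent direction of bias is shown. The damage is confined to the categorical dysfunction outcome and its secondary economic use. It is worth correcting before analysis, but it does not threaten the primary comparison.

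**What to change.** Make the main eGFR analysis the between-arm difference in mean annual slope from a linear mixed model with random intercept and slope. This extends the mixed model already named under Handling missing data. State that only the scheduled 4-monthly values enter, in both arms.

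If categories are kept for description or for the economic evaluation:

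- define them by a pre-set size of annual change, not by P or r²;
- make them mutually exclusive and exhaustive;
- say which earlier slope, if any, improvement is measured against;
- count graft failure as deterioration.

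A joint model of eGFR and graft failure could be a sensitivity analysis but need not be required.

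The cost is a change of wording in the protocol and analysis plan; the data are already being collected. The small downside is the loss of direct comparability with the cited study that used a similar regression rule.
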